### Part I: Protocol Summary

#### PROTOCOL SUMMARY

|                                 |                                                                                                                                                                                                                                                                                                                                                                                                                                                                                                                             |
|---------------------------------|-----------------------------------------------------------------------------------------------------------------------------------------------------------------------------------------------------------------------------------------------------------------------------------------------------------------------------------------------------------------------------------------------------------------------------------------------------------------------------------------------------------------------------|
| Title                           | Planning and SMS Reminders in the Promotion of a Healthy Diet                                                                                                                                                                                                                                                                                                                                                                                                                                                        |
| Location                        | Online                                                                                                                                                                                                                                                                                                                                                                                                                                                                                                                      |
| Study Objective (s)             | The aim of the study is to investigate the role of Planning and SMS reminders in the promotion of a more balanced diet.                                                                                                                                                                                                                                                                                                                                                                                                     |
| Study Design                    | Randomised Control Trial                                                                                                                                                                                                                                                                                                                                                                                                                                                                                                    |
| Study Population
Sample Size | 750 UK online users will be recruited, women and men between the ages of 30-60.                                                                                                                                                                                                                                                                                                                                                                                                                                             |
| Intervention                    | An Internet based study. Volunteers will be allocated into one of three different conditions: a) Control Group, b) Planning (=Implementation Intentions) and c) Planning and Short Message Service (SMS) Reminders. At Time 1, all subjects will be asked to fill out a set of questionnaires and then will be allocated into one of these three conditions. Four weeks later, subjects will come back to the website and report on changes in healthy eating, saturated fat intake and various psychological determinants. |
| Study Endpoints                 | The primary endpoint is:
a) Self-reported saturated fat intake (Margetts et al , 1989) and portion size changes
The secondary endpoint is:
a) To assess changes in other health related behaviours
b) To test the intervention effects on social cognitive measures (e.g. recovery and maintenance self-efficacy, action and coping planning) measured by the Health Action Process Approach model.                                                                                                             |
| Duration of Study               | Time 1: 30mins
Time 2: 30mins                                                                                                                                                                                                                                                                                                                                                                                                                                                                                            |

---

### Part I: Study Schematic:

| Phase 1                        | Phase 2                                                                                                                                             |
|--------------------------------|-----------------------------------------------------------------------------------------------------------------------------------------------------|
| 1) Subjects' Online Screening  | 1) Filling out Questionnaires on:

a) Saturated Fat Intake

b) Social Cognitive Determinants

c) Feedback on Information Received |
| 2) Signing Online Consent Form |                                                                                                                                                     |
| 3) Filling out Questionnaires  |                                                                                                                                                     |

|                                                                                                                                                          |                                                                                                                                                   |
|----------------------------------------------------------------------------------------------------------------------------------------------------------|---------------------------------------------------------------------------------------------------------------------------------------------------|
| 4) Random allocation of subjects in one of three conditions:
a) Control Group
b) Planning
c) Planning and Short-Message Service (SMS) Reminders |                                                                                                                                                   |
| 6) Re-direction to Virtual Surveys' website                                                                                                              | 2) Re-direction to Virtual Surveys' website

3) Payment of Subjects (stage 1: £5; stage 2: £10; payment received upon completion of Stage2) |

## 1. Study Overview

### 1.1 Background Information

A healthy diet, low in saturated fat and high in fibre, is a popular medical recommendation in helping people eat healthier. This type of recommendation would be particularly relevant to overweight or obese people, who may also want to lower or maintain a healthier cholesterol level. Most overweight people are likely to have good intentions to eat more healthily. However, good intentions are not always translated into action.

The emphasis of most current psychological models has been placed in identifying a number of factors that impact on intentions (motivational phase), leaving the translation between intentions into action less advanced (volitional phase). In this study, the focus is on the volitional phase of behaviour change. The Health Action Process Approach (HAPA) model (Schwarzer, 1999; Schwarzer et al, 2003; 2008) was chosen, since it addresses both the motivational phase and also the translation of motivation into behaviour. For a diagram of the HAPA model please see Appendix6.

In the HAPA model, a number of dimensions have been identified as playing an important role in the translation of intention into action namely a) action and coping planning and b) maintenance and recovery self-efficacy.

Maintenance self-efficacy is the confidence displayed by someone in dealing with barriers that arise once the behaviour has been initiated (Fuchs, 1997; Schwarzer & Fuchs, 1996; Luczynska & Schwarzer, 2003). Recovery self-efficacy addresses the experience of failure and recovery from setbacks. Some people tend to trust more their competence at getting back on track after they've derailed and to reduce harm than others (Marlatt, 2002).

The inclusion of action and coping plans also known as implementation intentions are instrumental in helping to bridge the gap between intention and behaviour. Research on action plans is not new. A meta-analysis of 94 studies (Gollwitzer & Sheeran, 2006) showed that implementation intentions had a positive effect of medium to large magnitude on goal achievement. It also provided some evidence that implementation intentions can change dietary behaviours.

Action Planning is more than just an extension of intentions because it includes specific situational parameters. Evidence shows that people are less likely to forget their intentions when they specify the when, where and how manner (Gollwitzer & Sheeran, 2006). Coping planning is a different type of planning. The focus here is on the anticipation of barriers and the generation of alternative behaviours to overcome them. People think of possible scenarios that would hinder from their intended behaviour 'If I plan to run on Sunday and the weather doesn't permit it, then I will go swimming instead', 'If I want to have a steak (unhealthy, high fat option) when I go out, then I will go for smoked salmon instead'.

Fine tuning of planning is essential to goal attainment. Though previous research was more concerned with proving the value of using plans, more research is now needed on the mechanisms that make a plan effective. A number of different formats have been used in the past. In experiments, subjects have been asked to form a specific plan in as much detail as possible paying particular attention to the situation in which they will implement these plans. For example, '...Please write below when, where and how you will make an appointment...' (Sheeran & Orbell, 2000). Though important these statements fail to create a strong cue-response relationship. 'If...then' statements could be more beneficial than the more global goal intention instructions in two ways. Firstly, 'if' statements make the critical situation more accessible to the user and thus shifting detection to the situation once encountered in the environment. Secondly, the 'then' component of the plan creates a stronger link between the situational cue and the goal-directed response, automatically initiating action when the critical situation is encountered. For example, Oettingen et al (2000) compared the effects of forming a goal intention alone to a goal intention furnished with an 'if..then' format. Whereas in both cases a concrete situation was specified, subjects in the 'if..then' condition adhered more closely to the time specified in their plan. Chapman et al (2008) also found that 'if..then' statements increased significantly fruit and vegetable consumption compared with the more global goal intention format in a student population. The present study is one of the few ones to test 'If...Then...' statements online within the context of healthy eating.

### **Short Message Service (SMS) Reminders**

It has been further argued that reminding people of their plans could enhance the impact of implementation intentions on behaviour (Gollwitzer et al, 1999; Sheeran et al, 2005). In a study by Prestwich et al (2008), subjects were randomly allocated into one of five conditions (Implementation Intentions and SMS reminders, Implementation Intentions, SMS reminders, and one of two Control Groups). In the follow-up four weeks later, results suggested a superiority of the combined condition in the frequency of exercise than the rest of the conditions, while neither the 'SMS reminders' or the 'implementation intention' groups were effective. In a later study, the same authors demonstrated that pairing Implementation Intentions with plan reminders or goal reminders increased the level of brisk walking relative to the control group. In addition, the goal reminder group lost more weight than the plan reminder group.

## 1.2 Rationale for Performing Study

The present study is an extension of a previous study conducted by Unilever Discover and approved by the Ethics Committee at the end of 2008. In this study we tested the effect of Heart-Age and the Planning tool on saturated fat intake. Heart-Age is a form of cardiovascular (CVD) risk communication. It is calculated as the age of a person with the same predicted risk but with all other risk factors levels in normal ranges. Heart-Age was found to be rather effective at helping people correctly perceive their CVD risk. Planning was more successful in changing behaviour e.g. lowering self-reported saturated fat intake. Effects were quite small in saturated fat changes and therefore it was necessary to start considering a) better measures of assessing behaviour changes and b) other ways of boosting the effects of implementation intentions on the outcome measures. This led to the present study, in which we combined planning with SMS reminders to test whether this could lead to stronger effects in behaviour than just planning on their own or nothing (Control Group).

## 1.3 Brief Description of Intervention

To the best of our knowledge there are no studies that have tested online the combined effects of planning with SMS reminders in a more complex behaviour such as dietary changes. In the present study, the aim was to test for differences on the effects of three different conditions on saturated fat intake and the purchase of products that contribute to lowering or helping maintain a healthy diet.

At **Time 1**, subjects will be invited to participate in the study by an online recruitment agency, which will also carry out the screening process. Once, subjects have been accepted in the study they will be randomly allocated into one of three conditions. In the most advanced condition, subjects will be asked to form implementation intentions and be reminded of their plans by SMS reminders over the course of the two weeks. In the second condition, they will be asked to form plans on how to eat healthier over the course of two weeks. All conditions will be asked to fill out questionnaires on: a) a self-reported dietary intake questionnaire (Margetts et al, 1989) and b) a self-reported questionnaire on various social cognitive variables (e.g. intentions, self-efficacy). The Control Group (CG) will be only asked to fill out these questionnaires at this stage. All three groups will receive educational information on the importance of a healthy diet low in saturated fat and the association between high cholesterol and being overweight. A coupon of a cholesterol lowering product, with 50p off the face value, will be posted to all participants as a reward for successfully completing baseline assessments.

At **Time 2 (4 weeks later)**, subjects will be invited to fill out again the same dietary measures of food intake and an extension of the psychological determinants' questionnaire. Study subjects will be rewarded for their participation in the study (£15). This will be upon completion of study phase 2.

## 1.4 Summary of risks and benefits to the subjects

### Benefits

The main benefit to the subjects:

- a) Starting a two-way interaction is crucial if we want subjects to start taking personal responsibility for their health. This study will attempt to engage them in the use of a planning tool to start making healthier eating choices and in the use of products and services that could help them maintain a healthier lifestyle.

### Risks

There is no perceived risk from engagement of participants with the planning tool or SMS reminders.

## **2. Study Objectives**

### **2.1 Primary Objectives**

#### **Objectives:**

The primary aim of the present study is to test the effects of Planning and SMS Reminders on saturated fat intake and purchase of a healthy product over a period of two weeks.

To assess the above, three questionnaires will be issued:

1. Margetts et al (1989) food frequency questionnaire
2. A two item self-reported saturated fat intake measure
3. Self-reported changes in portion sizes

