## **3. Study Design**

### **3.1. Design and Rationale**

This is a randomised, stratified between-groups study designed to assess the difference in saturated fat intake and coupon up-take between the three different experimental conditions; a) Planning and SMS reminders, b) Planning and c) Control Group. Subjects will be randomly allocated to one of these conditions and their responses will be measured by self-reported questionnaires.

Allocation to the subjects in the conditions will be stratified to balance by age group (30-45 years or 46-60 years), and gender. To help minimise any other imbalance effects obese (BMI $\geq$ 30) and non-obese participants (BMI $\geq$ 25), smokers and non-smokers will be also evenly allocated across the different cells.

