## Intentions: Stage 1/2

This question will be presented to subjects with the title 'Dietary Beliefs'

Please rate your intentions to change the following aspects of your diet over the next two weeks.

Over the next four weeks I intend to....

|                                              | Strongly
1 | Strongly
2 | Disagree
3 | 4 | 5 | Agree
6 | 7 |
|----------------------------------------------|---------------|---------------|---------------|---|---|------------|---|
| Replace high fat with lower fat alternatives |               |               |               |   |   |            |   |
| Eat smaller portions of high fat foods       |               |               |               |   |   |            |   |
| Reduce the amount of bad fats in my diet     |               |               |               |   |   |            |   |

## General Health Behaviours: Stage 2

This question will be presented to subjects with the title 'Your General Health Behaviours'

Compared to usual, over the last four weeks did you.....

|                                   | A lot
less
1 | About the
Same
2 | A lot
more
3 | 4 | 5 | 6 | 7 |
|-----------------------------------|--------------------|------------------------|--------------------|---|---|---|---|
| Drink alcohol                     |                    |                        |                    |   |   |   |   |
| Use Cholesterol lowering products |                    |                        |                    |   |   |   |   |
| Find you weigh                    |                    |                        |                    |   |   |   |   |

|                           |  |  |  |  |  |  |  |
|---------------------------|--|--|--|--|--|--|--|
| Smoke                     |  |  |  |  |  |  |  |
| Take up physical activity |  |  |  |  |  |  |  |
| Eat a well-balanced diet  |  |  |  |  |  |  |  |
| Choose lower fat foods    |  |  |  |  |  |  |  |

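### The stated aim and design include product purchase and coupon up-take, but no listed questionnaire item or endpoint measures either

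*Protocol*

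**What the plan says.** Three sections of the protocol name purchase or coupon up-take as something the trial tests.

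- Section 2.1 (Primary Objectives): besides an effect on saturated fat, the aim covers an effect on the "purchase of a healthy product over a period of two weeks". It continues "To assess the above, three questionnaires will be issued" and lists the food frequency questionnaire (FFQ), a two-item saturated fat measure and reported portion size changes.
- Section 1.3 (Brief Description of Intervention): the outcomes to be compared across conditions are saturated fat intake and "the purchase of products that contribute to lowering or helping maintain a healthy diet".
- Section 3.1 (Design and Rationale): the study is "designed to assess the difference in saturated fat intake and coupon up-take between the three different experimental conditions", and for the subjects, "their responses will be measured by self-reported questionnaires".

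The coupon is described once, in section 1.3. It gives 50p off a cholesterol-lowering product and "will be posted to all participants as a reward for successfully completing baseline assessments".

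The endpoint statements (Protocol Summary, section 7.1.1, section 11.1) name saturated fat intake and portion size changes as primary. The secondary endpoints in section 7.1.2 are other health behaviours, intention, self-efficacy, planning and reaction to the intervention. Among the other health behaviours, section 5.2 and the Stage 2 questionnaire in Appendix 3 include the item "Use Cholesterol lowering products", rated from 1 to 7 against usual over the previous four weeks.

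**The concern.** An aim can be answered only if something in the trial records the outcome it names. Here the aim and the design statement refer to buying a product or taking up a coupon, while the instruments and endpoints refer to eating. If the protocol is followed as written, there will be no purchase or redemption data to compare between arms.

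The final report would then have to pass over part of the stated primary aim, or present the product-use rating as if it were purchase. That rating and its analysis are pre-specified; calling it purchase would not be.

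**Working it through.** No arithmetic decides this point, so the check sets the sections side by side.

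| Place in the protocol | What it covers | Purchase or coupon? |
|---|---|---|
| Summary, objective | Planning and SMS reminders to promote a more balanced diet | No |
| 1.3, aim | Saturated fat; product purchase | Yes |
| 2.1, primary aim | Saturated fat; product purchase | Yes |
| 2.1, instruments | FFQ; two-item fat measure; portion changes | No |
| 3.1, design | Saturated fat; coupon up-take | Yes |
| 5.2, assessments | Fat, portions, other health behaviours, psychological measures, reactions | No (product use only) |
| 7.1.1 and 11.1, primary endpoint | Saturated fat; portion size | No |
| 7.1.2, secondary endpoints | Other health behaviours; psychological measures; reactions | No (product use only) |
| 11.2, analysis | Two-item measure, FFQ, portions, other health behaviours, psychological measures | No (product use only) |
| 11.3, sample size | Self-perceived saturated fat reduction | No |
| Appendix 1, schedule | Screening, questionnaires, payment | No |
| Appendix 3, questionnaires | All visible items | No (product use only) |

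**Could an existing item stand in?** There are two candidates.

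1. The Stage 2 product-use item matches the type of product on the coupon and falls under the planned analysis of variance. It rates perceived change in use relative to usual, is asked only at Time 2, and does not ask whether anything was bought or the coupon redeemed.
2. The FFQ is completed at both stages and includes low fat spread, polyunsaturated margarine and low fat cheese. Appendix 8 gives low fat spreads as an example of foods with added plant sterols. The FFQ records how often a food is eaten, and it does not separate sterol-enriched spreads from others.

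Each is related to the aim, but neither measures purchase.

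**Could coupon redemption supply the data?** Section 3.1 says responses come from questionnaires. The visible text describes no counting of redemptions and no link from a coupon to a subject or arm.

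**What a yes/no purchase question could detect, if one were added.** This is illustrative and does not affect the finding. Inputs: roughly 500 completers (section 6.2); equal allocation to three arms (assumed), so n = 500/3 ≈ 167 per arm; two-sided 0.05 and power 0.8 as in section 11.3; control rate p0 assumed. With p1 = p0 + Δ and p̄ the mean of p0 and p1, the detectable Δ satisfies

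Δ√n = 1.96√[2p̄(1 − p̄)] + 0.84√[p0(1 − p0) + p1(1 − p1)].

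For p0 = 0.20 and p1 = 0.336, p̄ = 0.268. The right side is 1.96 × 0.626 + 0.84 × 0.619 ≈ 1.75, and 1.75/√167 ≈ 0.135, in line with Δ of about 0.136. For assumed control rates of 10%, 20%, 30% and 50%, the detectable differences are about 11, 14, 15 and 15 percentage points.

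**The case against.** The strongest reply is that this is leftover wording with little effect on the trial. Three endpoint statements agree on saturated fat and portion size, the summary objective does not mention purchase, and the product-use item is already a secondary outcome with a planned analysis. The FFQ adds baseline and follow-up data on plausible products, and the phrase healthy product is never defined. Not all the material is visible either: the consent form and the study flow figure are not shown. The recruitment agency holds a log matching codes to names and addresses (Part III, section 2.1.6), so linking coupons to subjects was at least feasible.

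Most of this stands and limits the finding. The main comparisons are not threatened, and it would be wrong to say that nothing related is collected. It does not remove the contradiction. Purchase or coupon up-take is named in three sections, twice as an aim and once as what the study was designed to assess, and section 2.1 assigns it to questionnaires that do not ask about it.

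A further reply is that the statistical analysis plan, which is not shown, may deal with this. It can settle how data are analysed, but it cannot analyse data that no listed instrument collects. The absence of a power calculation or detailed analysis for purchase is a different matter and is not held against the protocol: analysis detail may sit in that plan, and a protocol need not power every outcome it names.

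**Conclusion.** The mismatch between objective and endpoint is real. As written, the trial cannot support or refute the purchase part of its stated aim. This affects one of the two outcomes named in section 2.1. That is a count of outcomes, not a statistical effect: no stated number is contradicted, and the saturated fat and portion size comparisons keep whatever validity and power they have.

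The conclusion rests on the visible protocol, including the Appendix 3 questionnaires, and on reading purchase and coupon up-take in their ordinary sense, as distinct from use or consumption.

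Three stronger readings are tempting, and the documents do not support them.

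- A reader might infer that the purchase wording leaves the primary outcomes unsettled. The summary, section 7.1.1 and section 11.1 all name saturated fat intake and portion size, and none names purchase.
- A reader might count the four-week window of the product-use item, against the two weeks in section 2.1, as a defect specific to purchase. The portion size and two-item fat measures also look back four weeks, and the FFQ covers the previous month. The two-week wording is a separate inconsistency that touches every instrument.
- A reader might infer that any later statement about product use would be post hoc. The item and its analysis are set in advance; only relabelling the result as purchase would be.

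**What to change.** Either of two changes removes the contradiction at the cost of protocol wording alone:

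1. Remove purchase and coupon up-take from sections 1.3, 2.1 and 3.1, so that the aim and design match the endpoints in sections 7.1 and 11.1. The coupon can remain as a reward. No procedure, endpoint, sample size or analysis changes.
2. Replace them with a secondary objective measured by the existing item "Use Cholesterol lowering products", worded as reported change in use over four weeks and not as purchase. This result must not later be described as purchase.

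If purchase or coupon up-take is wanted as such, add one Time 2 online question on whether the coupon was used or the product bought, list it as a secondary endpoint and compare it by arm. The cost is one extra self-reported item. On the illustrative figures above it could detect only fairly large differences between arms.

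Counting actual redemptions from coded coupons is possible but costs more than printing a code. The redemption records would have to be obtained and linked to subjects, which may require changes to the data protection text in section 9.4 and ethics approval of the amendment under Part III, section 2.2.
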